### Secondary Objectives

The usability of the tool will be measured through direct observation. The study staff will complete a checklist and note whether each participant was *successful* or *unsuccessful* in using the tool. They will also note whether the participant was able to complete the behavioral questions via electronic data collection.

User satisfaction will be recorded by a study team member via a series of yes/no questions to obtain an overall satisfaction score. Additionally, recommendations will be captured as free text and coded during analysis.

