## Methods

### Objectives

The primary objective of this study is to assess the participants’ risk behavior using an automatic machine-guided tool and compare these results to HIV outcomes. The secondary objectives are:

To evaluate the participants’ interaction with the tool in terms of effectiveness and efficiency, that is, successful/unsuccessful completion and difficulty using the toolTo assess the ability of the participants to correctly comprehend and complete specific behavioral questions on a digital platformTo understand user experience and satisfaction with the overall process and recommend improvements for machine-guided tool development

The study is registered on the South African National Clinical Trial Registry (www.sanctr.gov.za; DOH-27-042021-679) and was approved by the University of Witwatersrand Human Research Ethics Committee (HREC; ethics reference no. 200312) on August 20, 2020.

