### Demographic and Health Data Collection

All enrolled participants will have the following demographic data captured:

InitialsDate of birthAgeGenderNationality

The participant background information captured will include:

Employment status (employed/unemployed)Years of schooling and level (≤grade 7 primary schooling level/≥grade 8 primary schooling to ≤matric level/≥Technikon, university, and university plus)Reading/writing impairmentLanguage preferenceHIV status (if known)Approximate date of last HIV test

Participants may choose to report their medical health history, which will be documented and archived for statistical review. Information will include:

Self-reported HIV status:Unknown status/never been testedNegative statusSelf-reported medical conditions:DiabetesHypertensionVisual impairmentPregnancyOther

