#### Error and Failure Rates

Critical errors occur when participants make operational errors during interaction with the machine-guided tool. Project staff will aid participants, if needed, to ensure accurate completion of all behavioral questions that contribute directly to risk assessment scores.

The failure rate (cases where the risk score is high and the test result remains negative for both visits) will be identified and reported as the number or a percentage of failed cases of the total number of cases completed in the study.

It should be noted that failure due to critical errors (participants not being able to successfully complete the digital assessment) will not be included in the analysis.

The type of behavioral questions and the weighted score for each will be monitored and evaluated for continuous improvement and refinement purposes.

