#### Missing Data

The study will use electronic data capture for each participant, which requires that each question be completed before moving on to the next. This will eliminate the possibility of missing data during the data collection section of the study. Any participant record with missing results for a HIV test will be removed from the study.

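### Correct comprehension of the behavioral questions is a secondary objective, but the only measure tied to those questions is completion, which cannot by itself show understanding

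*Protocol article*

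**What the plan says.** The Objectives section lists three secondary objectives: interaction with the tool, comprehension and completion of the questions, and user experience. The second is to "assess the ability of the participants to correctly comprehend and complete specific behavioral questions" on a digital platform.

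The later Secondary Objectives section says how these are measured:

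- Use of the tool: "The usability of the tool will be measured through direct observation", with a staff checklist rating each participant successful or unsuccessful.
- The behavioral questions: "They will also note whether the participant was able to complete the behavioral questions via electronic data collection".
- Satisfaction: "User satisfaction will be recorded by a study team member via a series of yes/no questions", plus free-text recommendations coded at analysis.

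Three other places bear on what completion means. Under Missing Data, electronic capture "requires that each question be completed before moving on to the next". Under Error and Failure Rates, "Project staff will aid participants, if needed, to ensure accurate completion of all behavioral questions that contribute directly to risk assessment scores". Under Subject Tool Evaluation, the script read to the participant offers further explanation on request.

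Error and Failure Rates also leaves out of the analysis failures by participants who could not complete the digital assessment. It does not say whether this applies to the secondary objectives.

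**The concern.** The objective asks whether participants understood the questions and answered them correctly. The stated measure records whether they reached the end. A participant who misreads an item must still answer it to continue, and one who is stuck may be helped through. Both count as completed.

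The questionnaire answers are what the risk score is computed from. A misunderstood item therefore passes into the score and into the data used to train and validate the model, unless staff happen to catch it. If completion were the only evidence, a high figure could be read as showing that the questions are understood, with no data behind that reading. The matter affects one descriptive secondary objective directly. It does not alter the definition of the primary endpoint.

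**Working it through.** The documents give no completion rate, comprehension rate, target or precision for this objective, so there is no figure to reproduce. The check is mainly one of text against text.

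**Objective against measure**

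| Part of the objective | Measure in the Secondary Objectives section |
|---|---|
| Complete the questions | Staff note of whether the participant was able to complete them |
| Correctly comprehend the questions | None stated |

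The successful/unsuccessful checklist is described for use of the tool, and the yes/no items for satisfaction. Neither is described as testing whether a question was understood.

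**What completion can tell us (illustration; c and h are assumptions)**

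Let c be the share who understand, all assumed to complete. Let h be the share of those who do not understand but complete anyway, through forced entry or help. Then

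observed completion = c + (1 − c) × h.

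| True comprehension c | h = 0.95 | h = 0.50 |
|---|---|---|
| 50% | 0.50 + 0.50 × 0.95 = 97.5% (585 of 600) | 0.50 + 0.50 × 0.50 = 75% |
| 70% | 0.70 + 0.30 × 0.95 = 98.5% (591 of 600) | 0.70 + 0.30 × 0.50 = 85% |
| 90% | 0.90 + 0.10 × 0.95 = 99.5% (597 of 600) | 0.90 + 0.10 × 0.50 = 95% |

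A 40-point spread in comprehension shrinks to (1 − h) × 40 points of completion: 2 points at h = 0.95 and 20 points at h = 0.50.

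Nor can an observed figure be turned back into comprehension, because h is not measured. Completion of 97.5% fits c = 50% when h = 0.95. It also fits c = (0.975 − 0.50) / (1 − 0.50) = 95% when h = 0.50.

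**What the tool already collects**

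The question list under Subject Tool Evaluation asks about condom use (with an option for never having had sex), partners in the past 3 months, and sexual acts in the past 6 months (with a none option). These allow two checks:

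1. Never had sex, against any partner in 3 months or any act in 6 months.
2. At least one partner in 3 months, against no listed act in 6 months. The 3-month window lies inside the 6-month window, so these answers conflict unless the only act was one not listed.

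**Precision of such a check**

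Take n = 600 (Sample Size section) and an assumed contradiction rate of 10%:

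1.96 × √(0.10 × 0.90 / 600) = 1.96 × 0.01225 = 0.024, or about ±2.4 percentage points.

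This is the precision of the proposed check. It does not estimate any error in the current plan.

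**The case against.** The strongest reply is that the article condenses a fuller protocol and does not show the checklist or survey items. The Design section says the user is assessed for process success or difficulty, and a checklist might record requests for explanation. This stands in part: unseen forms may hold more. But the article does not leave the matter open. It has a section on measuring the secondary objectives, and there it ties completion alone to the behavioral questions. That is a measure badly fixed, beyond mere missing detail.

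A reader might infer more than the text supports:

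- **That completion is close to 100% by construction.** Forced entry stops skipping but does not stop a participant giving up, and Error and Failure Rates expressly foresees participants who cannot finish. Completion would be 100% by construction only if non-completers left the denominator of this endpoint, and the article does not say that they do.
- **That inconsistent answers would show as 0% under the current measure.** Completion does not estimate inconsistency, so it returns no figure for it. Inconsistency simply goes unmeasured.
- **That the study will declare the questions understood.** No section says so. The Results section promises a report on how easily participants interact with the platform.
- **That agreement between enrolment forms and the tool would measure comprehension.** Most of the shared items are demographic, and staff are to fill in the data collection forms. Education has three bands on the form and five differently defined options in the tool. "Approximate date of last HIV test" on the form meets time bands in the tool. Disagreement would mix recording, recall and category differences with misunderstanding, and would not test the sexual-behavior items.

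It is also fair to say that staff help is meant to secure accurate answers, which may reduce misunderstanding. But help given makes completion even less a measure of the participant's own comprehension.

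**Conclusion.** The concern holds in this form: comprehension is a stated objective, the only measure tied to the behavioral questions is completion, and forced entry and staff help push completion upward regardless of understanding. Completion alone cannot support a conclusion about comprehension.

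The direction follows from the text; the size is unknown, because the documents give neither a completion rate nor the share helped through. The 97.5% to 99.5% range rests on an assumed h of 0.95, and h = 0.50 gives 75% to 95%. The 2.4-point half-width rests on an assumed 10% rate with all 600 participants contributing. The point is worth correcting because the objective cannot be answered as written and a cheap partial remedy exists.

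**What to change.** 1. Report the rate of each of the two logical contradictions, and of either, with a confidence interval. Call it a partial, lower-bound indicator of miscomprehension or misentry: a misunderstood item can still be answered consistently, and a contradiction may also be a slip of entry. Confirm first that the application does not hide or block conflicting answers; the article describes no such control for these items.
2. Report completion separately, with everyone who started the tool in the denominator, including those who could not finish. State that the exclusion under Error and Failure Rates does not apply to this figure.
3. Have the observer already present mark on the existing checklist whether help was given, so that aided and unaided completion can be separated. Where help was not recorded, including for participants already seen, limit the conclusion to completion.
4. If enrolment-versus-tool agreement on demographic items is reported, label it a data-entry check only.

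Cost: the contradiction checks need a few lines of analysis on items already collected. The aided/unaided split needs one new checklist entry, because the article describes no record of assistance. The reported usability figure is likely to become less favorable.

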### Data Management

Data management will be undertaken by the HSTAR staff. Data will be collected on paper (questionnaires, informed consent forms) and on tablets (demographic data collection) and will be transmitted daily to the research site data staff. A data capturer will enter the paper-based data into an in-house-developed electronic database within 2 days. Data quality control will be managed daily by the project team.

#### Confidentiality

All documents, reports, and other records will be identified in a manner designed to maintain participant confidentiality. All records will be kept in a secure storage area with limited access. Clinical information will not be released without the written permission of the participant, except as necessary for monitoring and auditing by regulatory authorities.

The PI or designee and the study team may not disclose or use for any purpose other than performance of the study, any data, record, or other unpublished confidential information disclosed to those individuals for the purpose of the study. All computers are password-protected, and records can only be accessed by permitted study staff.

#### Record Retention

All correspondence relating to this study will be kept in appropriate study folders. Records of participants, source documents, and questionnaires pertaining to the study will be kept on file. Essential documents will be retained until at least 2 years after the last approval of a marketing application in an International Conference on Harmonization (ICH) region and until there are no pending or contemplated marketing applications in an ICH region or at least 2 years have elapsed since the formal discontinuation of product development. These documents will be retained for a longer period, if required by the applicable regulatory requirements. If an investigator moves, withdraws from the study, or retires, the responsibility for maintaining the records will be transferred to another person who is willing to accept the responsibility.

#### Data Reporting

Data reporting will be performed by the program manager and study consultants. A research report will describe the study area, study population, and execution of the research and present the study results. The report will present both qualitative and quantitative discussions on the outcomes of the study.

Biannual progress reports will be submitted to the University of the Witwatersrand Human Research Ethics Committee (HREC) for the duration of the study. Annual recertification will be obtained from the HREC. Upon completion or premature termination of the study, the PI will provide the HREC with a summary of the study’s outcome and any other regulatory authorities with any reports required.

### Other Study Procedures

#### Investigator Documentation

Prior to study commencement, the PI will be asked to comply with ICH E6(R1) 8.2 by providing the following essential documents, including but not limited to:

An original signed investigator agreement page of the protocol.An HREC-approved informed consent form, samples of site advertisements for recruitment for this study, and any other written information regarding this study that will be provided to the participants.HREC approval.Curriculum vitae of the PI and each investigator. They will be signed and dated by each investigator at study start-up, indicating that they are accurate and current.

#### Quality Control and Study Monitoring

Quality control of the study will be performed following the standard operating procedures developed for the study and those generic to the implementing organization. The project manager will assume overall responsibility for ensuring all procedures are adhered to and quality controlled.

A study monitor will be contracted. The study monitor will have the obligation to follow the study closely. In doing so, the study monitor will visit the study facility at periodic intervals, in addition to maintaining necessary telephonic and email contact. They will maintain current personal knowledge of the study through observation, review of study records and source documentation, and discussion of the conduct of the study with the PI and study staff.

All aspects of the study will be carefully monitored for compliance with applicable government regulation with respect to current ICH good clinical practice (GCP) guidelines and current standard operating procedures.

#### Protocol Amendments

Protocol amendments will be prepared by the PI. These amendments will be submitted in writing to the HREC for approval prior to participants being enrolled into the amended protocol, except where it is necessary to eliminate an immediate hazard to participants or where the changes involve only logistical or administrative aspects of the clinical study. This will be fully documented.

Examples of amendments requiring approval are:

A significant change in the study designAn addition or deletion of a test procedure for safety monitoring

The requirements for approval will in no way prevent any immediate action from being taken by the investigator or the sponsor in the interests of preserving the safety of all participants included in the study. If an immediate change to the protocol is deemed necessary by the investigator and is implemented by them for safety reasons, the PI will be notified and the HREC will be informed within 10 working days.

#### Protocol Violations and Deviations

A deviation from the protocol is an unintended or unanticipated departure from the procedures or processes approved by the HREC and agreed to by the PI or designee. Deviations usually have an impact on individual participants or a small group of participants and do not involve inclusion, exclusion, or primary endpoint criteria.

A protocol violation occurs when there is non-adherence to the protocol that results in a significant additional risk to the participant, when the participant or PI or designee fails to adhere to significant protocol requirements (inclusion and exclusion criteria) and the participant is enrolled without prior approval, or when there is non-adherence to regulations or some ICH GCP guidelines.

The PI or designee will document and explain in the participant’s source documentation any deviation from the approved protocol. The PI or designee may implement a deviation from or a change of protocol to eliminate an immediate hazard to trial participants without prior HREC approval. As soon as possible after such an occurrence, the implemented deviation or change, the reasons for it, and any proposed protocol amendments will be submitted to the HREC for review and approval.

Protocol violations and deviations will be documented by the clinical monitor throughout the course of monitoring visits. The PI or designee will be notified in writing by the monitor of violations and deviations. The HREC will be notified of all protocol violations and deviations in a timely manner.

#### Adverse Events and Adverse Device Event Reporting

Adverse events will be captured, and line listings provided. Any serious adverse event or adverse device event that may occur will be reported to the PI. Depending on the severity of the adverse event, the PI is obliged to report the event to the HREC. All serious adverse events will be reported by the PI.

#### Inspection of Records

The PI or designee and institutions involved in the study will permit study-related monitoring, audits, HREC reviews, and regulatory inspections by providing direct access to all study records.

#### Study Termination

Although there is every intention to complete the study, the implementing organization reserves the right to discontinue the study at any time for clinical or administrative reasons. The end of the study is defined as the date on which the last participant completes the last visit.

#### Dissemination

De-identified results will be disseminated through community engagements, study reports, and peer-reviewed publications and conference presentations. All outputs will be produced in compliance with donor requirements.

## Results

This study received ethical approval from the University of Witwatersrand HREC (ethics reference no. 200312) on August 20, 2020, and has been funded by the Bill & Melinda Gates Foundation (OPP 1204282). As an ongoing study, data collection has commenced and is expected to be completed in the second half of 2021. At the end of this study, we will be able to report on the performance and usability of the machine-guided tool, that is, the accuracy of the tool to identify people who are at high risk of contracting HIV and how easy participants find it to successfully interact with the digital platform. Lastly, the results of this study will report on user satisfaction and their recommendations for improvement. The results will be disseminated by the first quarter of 2022.

## Discussion

### Importance of Principal Findings

To the best of our knowledge, this would be the first evaluative report on a machine-guided tool for assessing the risk behavior associated with HIV acquisition in the South African context. South Africa has a high burden of HIV, and less than 90% of the population knows its HIV status [16]. Despite the large financial investment in the country, prevention of HIV infection remains a challenge [17]. In evolving economic landscapes and contexts that necessitate employment of innovative approaches to addressing HIV, machine guidance has the potential to offer a cost-effective, focused solution to identify priority populations for HIV prevention and treatment. Our study will provide evidence for this approach as a possible solution to tackling HIV risk and identification.

Machine guidance and artificial intelligence have proven useful in the health sector and are being used in many branches of medicine, including gastroenterology and hepatology [18], oncology [19,20], and infectious diseases [21,22]. For HIV, the potential benefits of engaging in machine-guided identification include immediate and private HIV test results, which may encourage frequent testing of individuals in high-risk groups who would otherwise refrain from testing due to the unknown risk factors associated with susceptibility to acquiring HIV. Although many health ministries make available free testing for HIV in a clinical setting, this machine-guided identification removes the need for spending time visiting a clinic and waiting for results, which is particularly critical where public testing facilities require long-distance traveling.

Nguyen et al [23] highlight the importance of understanding high-risk behaviors (eg, multiple concurrent partnerships, unprotected sex, and needle sharing) and demographic characteristics of people newly diagnosed with HIV/acquired immunodeficiency syndrome (AIDS). It is crucial for health programmers to consider this information as they design strategies for preventing HIV acquisition and transmission. With an earlier diagnosis, individuals are empowered to identify and modify their high-risk behaviors, potentially reducing the number of new HIV infections. This empowerment of consumers is not just limited to modifying lifestyle decisions but also involves being proactive in their health care decisions, which include adherence to clinic appointments and HIV treatment adherence (crucial to the prevention of viral rebound, treatment resistance, and the success of HIV management programs) [24,25].

The risk probability of contracting HIV may positively impact the effectiveness of universal testing and treatment by directing limited testing/treatment resources to the highest-risk groups, the number of people knowing their HIV status, the number of people linked to services, decision making and follow-up costs, reduction in duplication of tests, identification of high-risk self-harm cases, and PrEP initiation.

